#### Secondary outcome measures

• Ordinal 11-point box scales (0 = no pain, 10 = the worst pain possible) will be used to rate chest pain "now" (i.e. on the day of examination/completion of questionnaire) together with the following types of pain over the last week: "worst" and "average" chest pain, "average" thoracic spine pain, "average" cervical spine pain, "average" shoulder and arm pain.

• Improvement in chest pain and general health is rated by the participants using an ordinal 7-point scale using the categories: "Much worse", "worse", "a little worse", "no change", "a little better", "better", and "much better".

• The general health status is measures by the Medical Outcomes Study Short Form 36-item Health Survey (SF-36) [31,32]. The SF-36 comprises 36 items that can be combined into eight multi-item summary scores: physical functioning, vitality, bodily pain, mental health, social functioning, role limitation due to physical health and due to emotional problems, and general health perception, plus one item assessing a change in health over the past year.

• The Patient Specific Functional Scale is developed to assess functional limitations in a variety of clinical presentations [33]. Participants will be asked to identify three important activities with which they are having difficulties or are unable to perform because of their problem. In addition to specifying the activities the participants will be asked to rate on an ordinal 11-point box scale the current level of difficulty associated with each activity.

• As a surrogate for the assessment of pain and quality of life, we will use the indicators "number of visits to family doctor", "number of hospitalizations", and "amount of prescribed drugs". The data will be obtained from the comprehensive national Danish central registers. Non-prescription medication use for chest pain is measured using self-report questionnaires at 12 and 52 weeks.

• Information about adverse events and side effects will be collected for the therapy group by the treating chiropractor before and after each treatment session.

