#### Therapy group

Participants in the therapy group will be assigned to a chiropractor in their local community. Participating chiropractors will have a university chiropractic degree and at least five years of clinical experience. Each chiropractor chooses an individual treatment strategy based on a combination of their findings, the patient history, and pragmatic, routine practice. The treatment will be modified to accommodate the age and physical condition of each patient. The treatment must, however, include high velocity, low amplitude manipulation directed towards the thoracic and/or cervical spine in combination with any of the following: Joint mobilisation, soft tissue techniques, stretching, stabilising or strengthening exercises, heat or cold treatment, and advice. The protocol specifies up to ten treatment sessions of approximately 20 minutes, 1–3 times per week for four weeks, or until the patient is pain free if this occurs within less than four weeks. The type of manipulation technique will not be standardized, and the treating chiropractor can manipulate the lumbar spine if he/she determines to do so. The chiropractors record the types of treatment rendered at all sessions.

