#### Advice group

Advice is given in an approximately 15-minute session following the baseline assessment, and is directed towards promoting self-management. The participants are told that their chest pain generally has a benign, self-limiting course. The participants receive individual instructions regarding posture and two or three exercises aiming to increase spinal or muscle stretch based on clinical evaluation. They are advised to seek medical attention for re-evaluation (family physician, chest pain clinic or emergency department) in case of severe or unfamiliar chest pain. Further, the advice group is asked to refrain from seeking any manual treatment for the following four weeks.

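### Register counts of doctor visits, hospitalisations and prescribed drugs are named as a surrogate for pain and quality of life, although the assigned arm can partly determine them

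*Protocol article*

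**What the plan says.** The protocol article's section on secondary outcome measures states: "As a surrogate for the assessment of pain and quality of life, we will use the indicators". Three indicators follow: visits to the family doctor, hospitalisations and the amount of prescribed drugs. Their source is given as: "The data will be obtained from the comprehensive national Danish central registers".

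The Advice group section describes one session of about 15 minutes. Its content includes reassurance that the pain is generally benign, and this: "They are advised to seek medical attention for re-evaluation (family physician, chest pain clinic or emergency department) in case of severe or unfamiliar chest pain". It adds that "the advice group is asked to refrain from seeking any manual treatment for the following four weeks".

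The Therapy group section says: "The protocol specifies up to ten treatment sessions of approximately 20 minutes, 1–3 times per week for four weeks". The section also allows an earlier end once the pain has gone. It describes no re-evaluation advice of this kind, although advice in general is among the permitted components.

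The cost section handles similar data differently. Provider use, medication and hospitalisations for chest pain are treated there as health-care utilisation and cost. Study treatment is included, and every chiropractic visit in weeks 1-4 is recorded on a clinician form.

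**The concern.** An indicator can stand in for pain in a comparison of two arms only if it follows pain in the same way in both. Here the assigned intervention touches the step from having pain to making a counted contact. Advice patients are directed to counted services under a stated condition and asked to stay away from one uncounted service. Therapy patients regularly see a clinician whose sessions are not counted and to whom a recurrence can be mentioned.

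At stake is what may be concluded from a stated secondary outcome. A difference in register contacts would carry the authority of objective data and, under the label the article gives it, would be read as a difference in pain or quality of life. The temptation is real. The Discussion explains that pain intensity often falls within hours to days, which makes it a less than ideal primary outcome. The Background links residual chest pain to anxiety, fear of heart disease and re-admission, so some contacts are made for reassurance and do not measure pain alone.

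**Working it through.** **1. The arms side by side, as the article describes them**

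| Feature | Advice | Therapy |
|---|---|---|
| Told to seek re-evaluation at family physician, chest pain clinic or emergency department | Yes, if pain is severe or unfamiliar | Not described |
| Manual treatment, first four weeks | Asked to refrain | Up to ten sessions |
| Planned contact counted by the surrogate | None (one advice session) | None (chiropractor sessions not listed) |

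**2. What the surrogate needs**

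Let *e* be the mean number of pain episodes per patient, equal in both arms. Let *r* be the probability that an episode leads to a counted contact, with values r_A (advice) and r_T (therapy). Expected counted contacts per patient are e × r_A and e × r_T, so the difference is e × (r_A − r_T). With equal pain this is zero only if r_A = r_T. Nothing in the design makes them equal.

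**3. Which way could r move?**

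- Re-evaluation advice and the request to avoid manual care can raise r_A.
- Reassurance that the pain is benign can lower r_A.
- Chiropractor sessions can lower r_T by taking the place of a doctor visit, or raise it if the chiropractor sends the patient on.
- Prescribed drugs could follow doctor visits. This link is indirect, and the article does not describe it.

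The forces oppose one another, so the net sign is open.

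**4. Size, on assumed rates only**

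The article gives no visit or admission rates, so there is no figure of the plan to reproduce on this point. The only input from the article is 120 patients at 1:1, that is 120 / 2 = 60 per arm. Everything else here is assumed: equal pain, all excess in the advice arm, and a two-sided test at 0.05.

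For scale, if 10-30% of advice patients made one extra contact, that is 0.10 × 60 = 6 to 0.30 × 60 = 18 contacts, or 0.1 to 0.3 per patient.

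*Visit counts*, which is the form the article specifies. Visits were simulated as negative binomial with mean 2 or 4 and size parameter 1 or 2. A Poisson number of extra visits was added in the advice arm, and the arms were compared by t-test in 4,000 simulated trials per setting.

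| Extra visits per advice patient | Chance of a significant difference |
|---|---|
| 0 | 4-5% |
| 0.25 | 6-11% |
| 0.5 | 9-27% |
| 1.0 | 24-73% |

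*Any contact* (yes/no), a different endpoint, shown for comparison. With d = p2 − p1 and p̄ the mean of p1 and p2, the chance is Φ{[d − 1.96 √(2p̄(1−p̄)/60)] / √([p1(1−p1) + p2(1−p2)]/60)}. For 10% against 20%: (0.10 − 1.96 × 0.0652) / 0.0645 = −0.43, and Φ(−0.43) = 0.33.

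| Base share | +5 points | +10 | +15 | +20 |
|---|---|---|---|---|
| 10% | 13% | 33% | 58% | 79% |
| 20% | 10% | 24% | 45% | 67% |
| 30% | 8% | 21% | 40% | 61% |

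The distortion therefore runs from negligible to large, depending on rates the article does not state.

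**5. What is not touched**

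The primary outcomes are worst chest pain in the last week and patient-rated improvement. Neither uses register data. The confirmatory MANCOVA is described as covering patient-rated outcomes, which leaves the register counts out.

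**The case against.** The strongest reply is that the advice is conditional. It applies to severe or unfamiliar chest pain, so the visits it prompts are set off by pain and the counts still carry information about pain. That stands, and it rules out describing the advice as a general instruction to use these services. It does not restore the surrogate, because the same pain can still lead to a counted contact more readily in one arm than in the other.

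Second, the restriction on manual care is a request limited to four weeks, while questionnaire follow-up runs to 12 months. It may affect only a small part of the period counted. This also stands, and it is the reason for separating weeks 0-4 from the rest.

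Third, the therapy section is condensed and permits advice as a component, so therapy patients may receive similar information in practice. That is possible. Even then, the uncounted sessions would remain a difference between the arms.

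Fourth, the article names no analysis of the register indicators, measures pain and health status directly, and concedes in its Discussion that the design is not suited to correct for attention bias. All true. This limits the weight of the point. But the surrogate label is still in the text, and the concession is not applied to it.

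A reader might infer more: that the indicators will differ even with equal pain, and that the bias favours therapy. The article does not support this. It supports only that they can differ, since reassurance in the advice arm and onward referral from the therapy arm could work the other way. Nor do the two treatment sections contradict each other; they describe different arms.

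**Conclusion.** The point holds in a limited form. The three register indicators can be partly determined by the assigned arm, so a difference between arms cannot be interpreted as a difference in pain or quality of life. The conclusion rests on the arms differing as the article describes them. Neither the size nor the net direction of the distortion can be derived from the document, and the illustrative percentages rest wholly on assumed rates. The case is clearest for doctor visits and hospitalisations and weaker for prescribed drugs. It concerns the interpretation of one secondary outcome; the primary comparison is unaffected.

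**What to change.** In the section on secondary outcome measures:

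- Delete the statement that these indicators are a surrogate for pain and quality of life. Classify them as health-care use, as the cost section already does with similar data.
- Report them by arm alongside chiropractic contacts. Study sessions are already on the clinician treatment forms, and other provider use is in the questionnaires at weeks 12 and 52.
- Show weeks 0-4 separately from later follow-up, assuming the register records carry dates. The arms differ by design in the first period.
- Base conclusions about pain and quality of life on the pain scales, the SF-36 and the EuroQol, all of which are already collected.

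No change to either intervention is proposed. The cost is a wording change and one added tabulation, with no new data collection. The trial gives up a register-based claim about pain, which is a small loss given the direct measures.

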### Outcome measures

The outcomes are measures by self-report questionnaires that are collected at baseline, after four weeks (CTA positive patients only), and after three and 12 months (all patients) (see Figure 1).

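### Adverse events are solicited in the therapy arm only, at treatment sessions, by the treating chiropractor, so the trial obtains no between-arm adverse-event comparison beyond crude indirect indicators

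*Protocol article*

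**What the plan says.** Under Secondary outcome measures, the protocol article gives one sentence on harms: "Information about adverse events and side effects will be collected for the therapy group by the treating chiropractor before and after each treatment session". It names the arm, the collector and the occasions.

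Under Therapy group, those occasions are bounded: "The protocol specifies up to ten treatment sessions of approximately 20 minutes, 1–3 times per week for four weeks", with an earlier end if the patient becomes free of pain.

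Under Advice group, contact is a single visit: "Advice is given in an approximately 15-minute session following the baseline assessment, and is directed towards promoting self-management". The content is partly physical: "The participants receive individual instructions regarding posture and two or three exercises aiming to increase spinal or muscle stretch based on clinical evaluation". These patients are told to seek medical care for severe or unfamiliar chest pain, but nothing says that such episodes are recorded as adverse events.

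Under Outcome measures, self-report questionnaires are collected at baseline and then "after four weeks (CTA positive patients only), and after three and 12 months (all patients". Every randomised patient is CTA positive, so both arms receive all of these questionnaires. Adverse events are not among the items described for them.

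Secondary outcome measures also lists family-doctor visits, hospitalizations and prescribed drugs from national registers, without restriction to one arm. Their stated purpose is not safety: "As a surrogate for the assessment of pain and quality of life, we will use the indicators".

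**The concern.** An adverse-event rate is informative about a treatment when it can be set beside the rate in comparable patients who did not receive it. These patients have just been discharged after an acute chest pain episode. The Background section says that about three quarters of patients with undiagnosed chest pain go on to have residual pain. Flares, soreness and new symptoms will therefore occur under either allocation, and the advice arm has stretching exercises that could cause reactions of their own. Its rate cannot be taken as zero.

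Two features of the therapy-arm record add to the problem. The recorder delivers the treatment, so is not independent of it. Recording also depends on attendance: a patient who stops coming, possibly because of a reaction, is not asked again, and a delayed reaction to the last session has no later session at which to be reported.

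The article expects its results on manual treatment to inform clinical decisions and policy. As written, benefit is measured alike in both arms, while adverse events are measured in one.

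**Working it through.** The article gives no figure for harms, so there is none to reproduce. Its one design figure, 81% power with 120 patients, concerns improvement in chest pain and does not bear on this point.

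**Step 1. What is solicited in each arm.**

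| | Therapy group | Advice group |
|---|---|---|
| Adverse events solicited | Yes | Not described |
| Collector | Treating chiropractor | None described |
| Occasions | Before and after each session | None described |
| Time covered | Up to four weeks, less if pain free | None |
| Questionnaires at 4 weeks, 3 and 12 months | Yes, no adverse-event items described | Yes, no adverse-event items described |

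Maximum solicited enquiries per therapy patient: 10 sessions × 2 = 20. This is a ceiling, since sessions are capped at ten and may stop early. The advice-group figure on the article's text is 0.

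**Step 2. What can be estimated.** A between-arm risk difference is p(therapy) − p(advice). With adverse events ascertained in one arm, p(advice) has no data, so neither a difference nor a ratio can be formed at any sample size. What remains is a one-arm rate in about 60 patients (120 at 1:1 allocation gives 120/2 = 60).

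**Step 3. What two-arm data exist.** The following are held on both arms and extend past the last session:
- the 7-point change ratings for chest pain and general health, each with three worsening categories;
- the pain scales for chest, thoracic spine, cervical spine, and shoulder and arm;
- SF-36;
- register hospitalizations and family-doctor visits;
- self-reported utilization and lost work or activity days at 12 and 52 weeks.

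They permit crude comparisons of worsening and of events that lead to health-care contact. They do not capture a transient reaction that prompts no contact. The regional pain items ask for average pain over the last week, so a reaction in weeks 1 to 3 that has settled would not show at 4 weeks.

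**Step 4. What equal ascertainment would buy.** With n = 60 per arm, two-sided α = 0.05 (assumed; the article states none), advice rate p₂, therapy rate p₁ = p₂ + d and p̄ = (p₁ + p₂)/2:

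power = Φ{[d − 1.96·√(2p̄(1 − p̄)/60)] / √([p₁(1 − p₁) + p₂(1 − p₂)]/60)}.

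Example with p₂ = 0.10 and d = 0.204: p̄ = 0.202, the first root is 0.0733 and the second is 0.0709. So (0.204 − 1.96 × 0.0733)/0.0709 ≈ 0.85, and power ≈ 80%.

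| Assumed advice-arm rate | Increase detectable at 80% power |
|---|---|
| 5% | 17.5 points |
| 10% | 20.4 points |
| 20% | 23.6 points |

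The advice-arm rates are assumptions; the article gives none.

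**The case against.** The strongest reply is that the trial is not blind to harm in the advice arm. The sources in step 3 cover both arms, and the register data depend neither on the treating chiropractor nor on patient recall. A reader might infer from the adverse-event sentence that no comparison of harm is possible at all, or that everything after the last session is lost. The documents do not support either reading: a crude comparison of worsening and of hospitalizations is available, and it runs to 12 months. What is missing is a comparison of adverse events and side effects as such. The register indicators are offered as surrogates for pain and quality of life, not as harms.

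Second, the article promises no safety comparison. Its aims are prevalence, the diagnostic process, relative effectiveness and cost-effectiveness, and a session log suits a description of immediate treatment reactions. That stands, and the log should be kept. But adverse events are listed as an outcome of a randomised trial, and a one-arm record invites a safety conclusion that it cannot carry.

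Third, a reader might size the defect by the upper limit after zero events in 60 patients: 1 − 0.05^(1/60) = 4.9%, one-sided 95%. That limit reflects the number treated. It would be the same with perfect collection in both arms, so it does not measure this defect.

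Fourth, the direction of bias is not established. Repeated asking may raise the therapy count, while reporting to the treating clinician may lower it, and the article gives no figure for either effect.

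Finally, a condensed article can omit detail. Here, however, the text states the arm, the collector and the timing. That collection is confined to the therapy group is an inference from that sentence and from the absence of any other description.

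**Conclusion.** The point holds as a stated design weakness. Followed as written, the plan solicits adverse events in one arm, through the clinician giving the treatment, up to 20 times over at most about four weeks. It describes none in the other arm. No between-arm adverse-event estimate follows from that, whatever the sample size, and the therapy-arm count mixes treatment reactions with natural course. Only crude indirect comparisons remain, from data not labelled as harms.

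This does not affect the primary efficacy analysis. It limits what may be said about safety. The conclusion assumes that the full protocol adds no adverse-event items to the questionnaires, and that the 120 patients divide at about 60 per arm.

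**What to change.** Add the same short set of adverse-event items, identically worded for both arms, to the self-report questionnaires at 4 weeks, 3 months and 12 months. State that any between-arm comparison of harms will use that common source, supported by register hospitalizations. Keep the chiropractor's session log, report it separately as a description of the therapy arm, and draw no comparative safety claim from it.

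The cost is a few items in existing questionnaires and a small amendment; treatment is unchanged. There are two limits. The trial began in 2006 and is under way, so patients already past a given questionnaire will lack its items, and the comparison will be incomplete and should be reported so. With about 60 per arm it will also be coarse, as step 4 shows, so it should be presented as estimates with confidence intervals and not as evidence of equal safety. If the items can no longer be added, the minimum is to report the session log as one-arm data and to say that adverse events were not solicited in the advice group.

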### Predictors of outcomes

• Prior to commencing treatment, patients are asked to rate their expectation towards treatment benefits on a 5-point scale, with responses ranging from "getting much worse" to "getting much better".

• The Brief Illness Perception Questionnaire (B-IPQ) assesses perception of illness by asking patients for their own belief about their condition [34]. The B-IPQ consists of eight items that can be combined into five cognitive components: Identity, cause, time-line, consequences and cure/control. These components together make up the patient's perception of their illness. All eight items are measured using ordinal 11-point box scales.

### Health care cost/Cost-effectiveness analysis

Direct health care cost, direct non-health care cost and indirect cost are used in the economic evaluation as an indicator of cost-effectiveness. Cost data are collected through patient self-report questionnaires at 12 and 52 weeks. Direct costs for each patient will represent the one-year aggregated chest pain related health care costs based on utilization and estimated costs. Health care utilization (within and outside the study) is measured using standardized clinician treatment forms (each chiropractic visit, weeks 1–4), and patient rated self-report questionnaires (baseline and weeks 12 and 52). Direct health care costs include costs related to study treatment, non-study health care health provider use, medication utilization, and hospitalizations for chest pain. Indirect costs of productivity loss is measured by patient self-report (weeks 12 and 52) using questions that measure lost or impacted work or activity days due to chest pain. The EuroQol 5D (modified version) [35,36], a multi-attribute, patient self-report utility scale measuring five dimensions (mobility, self-care, usual activities, pain/discomfort, and anxiety/depression), is used as the cost-utility index. It is measured at baseline and weeks 4, 12, and 52.

